### Outcome

The primary outcome is the rate of STR ≥ 70% on surface electrocardiogram (ECG) at 90 min after PCI. The secondary outcomes are the degree of STR, TIMI flow grade, TIMI myocardial perfusion grade, LVEF, N-terminal prohormone brain natriuretic peptide, high-sensitivity C-reactive protein, and infarct size expressed as area under the curve for cardiac troponin I and for creatine kinase MB. The MACE (defined as a composite of nonfatal stroke, nonfatal MI, target lesion revascularization, urgent stent thrombosis, and all-cause death) will be recorded, as well as the hospital readmissions for heart failure or cardiac angina. Health quality will be assessed by using the 12-item Short Form Health Survey [28].

The safety outcomes include bleeding events measured with Platelet Inhibition and Patient Outcomes (PLATO) criteria within 48 h and 30 days, as well as adverse events (AEs) during the study period. Abnormal change in routine blood test results will also be monitored during the study. In addition, psychologic status and dietary patterns of patients will be collected as relevant indicators using the Hamilton Depression Scale [29] and the Food Frequency Questionnaire [30]. A study schedule and evaluation of outcomes are provided in Table 1. Centralized, blinded reviews of angiographic data and ECG recordings will be conducted by two physicians, respectively.

**Table 1 Tab1:** Outcome evaluation time points

Outcomes	Baseline	Preoperation	Postoperation (immediately)	30 min	60 min	90 min	6 h	12 h	18 h	24 h	36 h	48 h	72 h	7 d	30 d
Subject characteristics	•	–													
STR	•	–		•			–			•	–			•	–
TIMI flow grade TMPG	–	•		–											
LVEF	–									•	–			•	
cTnI, CK-MB	•	–					•							–	
NT-proBNP	•	–								•	–	•	–	•	
hs-CRP	•	–								•	–		•		
MACE	–														•
Hospital readmission	–														•
SF-12	•	–													•
Bleeding events	–											•	–		•
Adverse events	•														
Routine blood test	•	–													•
HAMD-17	•	–												•	
FFQ	•	–													

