### Sample size

Based on the results of the previous investigation [31–33], a sample size of 336 participants was estimated to provide 80% power to detect an absolute difference of 20.2% between the combined Danhong group and control in the rate of STR ≥ 70% measured at 90 min after PCI at a two-sided significance level of 0.05, assuming an STR ≥ 70% rate of roughly 50% for the control group and 20% loss to follow-up.

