### Randomization

In each center, the enrolled patients will be randomly assigned to the control group of conventional treatment, the preoperative-Danhong group, or the postoperative-Danhong group, allocated by the central randomized management system according to a ratio of 1:1:1. The randomization sequence will be generated in varying block sizes and stratified by center. After informed consent is obtained, the researcher will log into the central randomized management system of the network and choose the center as the stratified factor. The central randomized management system will generate a unique identification code and random number for each patient, which can be used to represent the identity of the patient and indicate the therapeutic intervention.

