### Statistical analysis methods

The null hypothesis is that the rate of STR ≥ 70% at 90 min after PCI will be the same for the combined Danhong group and the control group. The primary outcome analysis will use the Cochran-Mantel-Haenszel test to compare the rate of STR ≥ 70% at 90 min after PCI between the combined Danhong groups and the control group. If the result of this analysis is significant, hierarchical testing will be used to compare the preoperative-Danhong group with the control group, the postoperative-Danhong group with the control group, and the preoperative-Danhong group with the postoperative-Danhong group.

For other categorical variables, comparisons between treatment groups will be done using Fisher’s exact test or the chi-square test as appropriate. Continuous variables will be compared using the *t* test or Wilcoxon rank-sum test as appropriate. Chi-square or Fisher’s exact tests will be used to compare the frequency of AEs between groups.

The intention-to-treat population, including all randomized patients, will be used for all efficacy and safety analyses. All analyses will be performed using SAS version 9.4 software (SAS Institute Inc), with a two-sided *P* value less than 0.05 considered significant. No interim efficacy analysis will be performed.

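### Continuous secondary outcomes are tested without centre or the collected baselines: valid and slightly conservative, but precision is lost by an amount the document does not let us fix

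*Protocol article*

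**What the plan says.** All references are to the protocol article.

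- **Statistical analysis methods**, continuous outcomes: the sentence that begins "Continuous variables will be compared using the" reads in full "Continuous variables will be compared using the *t* test or Wilcoxon rank-sum test as appropriate". No covariate, stratum, change score or model is named. Categorical outcomes other than the primary get plain chi-square or Fisher tests.
- **Statistical analysis methods**, primary outcome: "The primary outcome analysis will use the Cochran-Mantel-Haenszel test to compare the rate of STR ≥ 70% at 90 min after PCI". This is a stratified type of test, but its strata are not named.
- **Randomization**: "The randomization sequence will be generated in varying block sizes and stratified by center", with allocation "according to a ratio of 1:1:1". Centre is the only stratification factor in the document.
- **Outcome**: "The secondary outcomes are the degree of STR, TIMI flow grade, TIMI myocardial perfusion grade, LVEF, N-terminal prohormone brain natriuretic peptide", followed by hs-CRP and the cTnI and CK-MB areas under the curve. SF-12 is assessed in addition.
- **Table 1** marks a baseline assessment for STR, cTnI, CK-MB, NT-proBNP, hs-CRP, SF-12 and HAMD-17. It marks none for LVEF. As the extracted table reads, NT-proBNP and hs-CRP each have more than one follow-up time.

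**The concern.** When randomisation is balanced within centre, differences between centres cancel out of the comparison of arms. A two-sample test still counts that between-centre variation as noise, so its standard error is too large whenever centres differ. Similarly, where an outcome is predicted by its own baseline, a test that leaves the baseline out carries variation that could have been explained. It also leaves any chance baseline difference between arms in the estimate.

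At stake is the precision of the biomarker and quality-of-life comparisons. The sample size is justified for the primary binary outcome only, so the secondary comparisons, including the preoperative versus postoperative contrast, have whatever power the analysis can extract. The text names specific tests. It is therefore a stated choice of method, not a detail left to an analysis plan.

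**Working it through.** **1. The plan's own figure.** The document gives no power or precision figure for any continuous outcome, so there is none to reproduce. The 336 in Sample size concerns the primary binary outcome and is used here only for arm size: 336/3 = 112.

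**2. Inputs.** From the document: 112 per arm and testing "at a two-sided significance level of 0.05". Assumed, because the document gives neither: r, the baseline to follow-up correlation, from 0 to 0.7; and ICC, the share of outcome variance lying between centres, from 0 to 0.10.

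**3. Formulas.** Adjusted variance relative to the variance used by the crude test: f = (1 − r²)(1 − ICC). Take a comparison with nominal 80% power under the crude test, so that effect/SE = 1.960 + 0.842 = 2.802. Adjusted power is then Φ(2.802/√f − 1.960).

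| r | ICC | f | SE reduction | Adjusted patients per arm matching 112 crude (112 × f) | Power |
|---|---|---|---|---|---|
| 0 | 0 | 1.00 | 0% | 112 | 80.0% |
| 0.3 | 0 | 0.91 | 4.6% | 102 | 83.6% |
| 0.5 | 0 | 0.75 | 13.4% | 84 | 89.9% |
| 0.7 | 0 | 0.51 | 28.6% | 57 | 97.5% |
| 0 | 0.05 | 0.95 | 2.5% | 106 | 82.0% |
| 0 | 0.10 | 0.90 | 5.1% | 101 | 84.0% |
| 0.5 | 0.05 | 0.71 | 15.6% | 80 | 91.3% |

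The 80% in the centre rows is nominal, computed from the crude standard error. Because stratification has already removed centre from the true sampling error, the crude test's actual power at ICC 0.05 is Φ(0.842/√0.95) = Φ(0.863) = 80.6%. The real gain from centre alone is therefore nearer 1.4 points than 2.

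**4. Validity of the crude test.** Its true type I error is 2[1 − Φ(1.960/√(1 − ICC))]. At ICC 0.05 this is 4.4%, and at ICC 0.10 it is 3.9%. Both are below 5%.

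**5. Simulation check.** Assumed: 10 centres, 90 evaluable patients per arm, two arms, ICC 0.05, 2,000 runs.

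| r | Standardised effect | Crude t test rejects | Adjusted for baseline and centre rejects |
|---|---|---|---|
| 0 | 0.4 | 76.5% | 78.1% |
| 0.3 | 0.4 | 78.0% | 82.7% |
| 0.5 | 0.4 | 77.1% | 88.5% |
| 0.5 | 0 | 4.5% | 4.4% |

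Adjustment cost nothing when the baseline was uninformative, and both tests held their level.

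**6. Chance imbalance.** The baseline difference between two arms of 112 has SE √(2/112) = 0.13 SD, so a 95% range of about ±0.26 SD. At r = 0.5, an imbalance at that limit moves the crude outcome difference by 0.5 × 0.26 = 0.13 SD.

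**7. Which outcomes the baseline argument reaches.**

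- NT-proBNP, hs-CRP and SF-12: baseline collected, so the argument applies directly.
- Degree of STR: already expressed relative to the baseline ECG, so only centre clearly applies.
- LVEF: no baseline in Table 1, so centre only.
- cTnI and CK-MB AUCs: the baseline sample may be the first point of the curve, and the document does not say. Centre applies; baseline applies only if that sample lies outside the AUC.
- HAMD-17: collected as a related indicator, not a secondary outcome.

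**The case against.** The strongest reply is that nothing here is an error. The t and Wilcoxon tests are valid under randomisation, and their standard errors already allow for chance baseline imbalance on average. What remains is a preference for efficiency, in outcomes that do not decide the trial. That is right about validity and limits the weight of the point. It does not remove the point, because a known stratification factor and baselines already collected are left unused.

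A second reply is that a journal article condenses, and that its one sentence does not say whether raw values, logged values or changes from baseline are tested. This stands in part, since a change score would use the baseline. It would still omit centre. With equal variances at both times, its variance relative to the raw follow-up value is 2(1 − r), which is 1.40, 1.00 or 0.60 at r = 0.3, 0.5 or 0.7, against 0.91, 0.75 or 0.51 for ANCOVA.

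A third reply is that the gain may be close to zero, because biomarkers drawn early in STEMI may correlate weakly with later values. This stands, and is why the range starts at r = 0.

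A fourth is that stratifying every binary outcome by centre suits rare events poorly: the number of centres is not given, and strata without events contribute nothing. This also stands, and exact tests for such outcomes are reasonable.

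**Conclusion.** The point holds as one of lost precision in secondary outcomes. The named tests ignore the stratification factor for every continuous outcome, and they do not take baseline as a covariate for NT-proBNP, hs-CRP and SF-12, where it is available. The variance given up runs from nothing (r = 0) through 9% and 25% to 49% (r = 0.3, 0.5, 0.7). Centre adds about two points of nominal power at ICC 0.05. Every one of these figures rests on an assumed correlation or ICC.

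A reader might infer more, and the documents do not support it:

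- **Biased results or inflated false positives.** The crude tests are, if anything, conservative.
- **A compromised primary result.** The primary outcome has its own test of stratified type, although its strata are not named.
- **Baselines wasted across all continuous outcomes.** LVEF has none, degree of STR already incorporates its baseline, and the AUCs may do so.
- **Close to half the information discarded.** That is only the favourable end of an assumed range.

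**What to change.** Amend Statistical analysis methods, before the database is locked, as follows.

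- **NT-proBNP and hs-CRP** (log scale where skewed) **and SF-12**: ANCOVA, or a mixed model where there are repeated follow-up times, with arm, centre and the baseline value.
- **LVEF, degree of STR, and the cTnI and CK-MB AUCs**: adjust for centre. Add baseline cTnI or CK-MB only if that sample is not part of the AUC, and state whether it is.
- **Binary secondary outcomes that are not sparse**: a centre-stratified test. Keep exact tests for rare events such as MACE.
- **Sensitivity analysis**: retain the t, Wilcoxon and unstratified categorical tests.

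The cost is revised wording and some extra programming. No new data, visits or patients are needed. The article reports recruitment as still under way, so at that stage the change could be specified in advance.

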### Intervention

Patients will receive aspirin 300 mg and clopidogrel 600 mg (or ticagrelor 180 mg) before PCI. Postoperative treatments will include antithrombotic medication (aspirin 100 mg daily with clopidogrel 75 mg daily or ticagrelor 90 mg twice daily), anti-myocardial ischemia (β-blockers, nitrates, calcium antagonists), inhibition of cardiac remodeling (angiotensin-converting enzyme inhibitor, angiotensin receptor blocker, aldosterone receptor antagonist), and lipid control (atorvastatin 20 mg daily). These are all serving as conventional treatment for patients with STEMI. Patients in the preoperative-Danhong group will additionally receive Danhong Injection treatment (40 ml with 250 ml of saline, intravenous drip infusion) as early as possible before PCI and continue to the seventh day, once per day. Patients in the postoperative-Danhong group will additionally receive Danhong Injection treatment (40 ml with 250 ml of saline, intravenous drip infusion) right after PCI and continue to the seventh day, once per day.

It should be noted that any Chinese medicine related to the treatment of coronary heart disease should not be taken orally, intravenously, or intracoronally during the study. According to the hospital centralized monitoring data [27], the following drugs should be avoided in combination with Danhong Injection: potassium magnesium aspartate, thymosin, celecoxib, and bisoprolol fumarate. The patients will stay in the hospital during the intervention period, which is convenient to monitor adherence to the intervention.

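### Safety is analysed only in all randomized patients, so Danhong-assigned patients who are never infused stay in the Danhong safety denominators; a treated-patient safety set should be reported alongside

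*Protocol article*

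**What the plan says.** The protocol article, under Statistical analysis methods, names one population for everything: "The intention-to-treat population, including all randomized patients, will be used for all efficacy and safety analyses". In the same section, chi-square or Fisher's "exact tests will be used to compare the frequency of AEs between groups". No treated or safety population and no grouping by treatment received appears anywhere. The article does not write out that patients are analysed in their assigned arm, but that is the ordinary meaning of intention-to-treat and nothing in the text modifies it.

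The safety outcomes, under Outcome, are "bleeding events measured with Platelet Inhibition and Patient Outcomes (PLATO) criteria within 48 h and 30 days", adverse events over the study period, and abnormal changes in routine blood tests.

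Three statements fix the order of events. Under Randomization: "After informed consent is obtained, the researcher will log into the central randomized management system". Under Intervention, the preoperative arm is dosed "as early as possible before PCI and continue to the seventh day, once per day", and the postoperative arm "right after PCI and continue to the seventh day, once per day". The Intervention section adds that patients remain in hospital throughout the dosing period. The Discussion states that there is no placebo and no double-blinding.

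**The concern.** Because one arm is dosed before PCI, allocation must be made before PCI. The other Danhong arm is dosed only afterwards. Between allocation and first infusion a patient may die, withdraw, or turn out not to have PCI. The treatment is open, so staff may also hold back an infusion knowing the assignment. A patient who never receives Danhong for any of these reasons still counts as a Danhong patient for bleeding, adverse events and blood tests.

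For a superiority claim on efficacy, such dilution is usually conservative. For harm it can work the other way: a smaller observed difference makes the test drug look safer. Bleeding is a named outcome, and all patients are on dual antiplatelet therapy. The incidence among patients who actually received the drug is also not reported under this rule.

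**Working it through.** **Inputs from the article.** Total sample 336 (Sample size), allocated "according to a ratio of 1:1:1" (Randomization). This gives 336 / 3 = 112 per arm, so 224 in the two Danhong arms and 112 controls. Two-sided significance level 0.05.

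**Inputs not in the article, taken as assumptions.** The never-exposed share u, and the event risks in control patients (p_C), exposed Danhong patients (p_E) and never-exposed Danhong-assigned patients (p_U). The plan states no figure on any of these, so there is no figure of its own to reproduce.

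**Step 1. Observed Danhong risk under the stated rule.**

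Danhong risk = (1 − u) × p_E + u × p_U

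If p_U = p_C, the observed excess over control is (1 − u) × (p_E − p_C). The excess shrinks by exactly the share u. For example, with p_C = 5%, p_E = 10% and u = 10%: 0.90 × 0.10 + 0.10 × 0.05 = 0.095, an excess of 4.5 points.

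**Step 2. Size over a range of u, with p_U = p_C.** Power uses the normal approximation for two proportions, with pooled variance under the null and unpooled under the alternative, for the combined Danhong arms against control. The exposed-only column compares 224 × (1 − u) infused patients with 112 controls.

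| u | Excess, 5% vs 10% (points) | Power, all randomized | Power, exposed only | Excess, 10% vs 20% (points) | Power, all randomized | Power, exposed only |
|---|---|---|---|---|---|---|
| 0 | 5.0 | 32.9% | 32.9% | 10.0 | 65.4% | 65.4% |
| 2% | 4.9 | 31.9% | 32.8% | 9.8 | 63.8% | 65.2% |
| 5% | 4.75 | 30.5% | 32.7% | 9.5 | 61.3% | 64.8% |
| 10% | 4.5 | 28.0% | 32.5% | 9.0 | 57.0% | 64.1% |
| 20% | 4.0 | 23.5% | 31.9% | 8.0 | 48.2% | 62.5% |

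At u = 2–5% the loss of power is about 1 to 4 points. At u = 10–20% it is about 5 to 17 points. The comparison of a single Danhong arm with control has fewer patients and would have less power still.

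**Step 3. The direction depends on p_U.** Keep p_C = 5% and p_E = 10%, but suppose the never-infused are sicker, with p_U = 20% (assumption).
- u = 5%: 0.95 × 0.10 + 0.05 × 0.20 = 0.105, an excess of 5.5 points.
- u = 10%: 0.90 × 0.10 + 0.10 × 0.20 = 0.110, an excess of 6.0 points.

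The observed harm is now larger than the 5.0 points in exposed patients, because events in patients without the drug are counted against it.

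**Step 4. Why the never-infused should not be moved to the comparator.** Same assumptions as Step 3, comparing any infusion with none.
- u = 5%: 224 × 0.05 = 11.2 patients move. Comparator risk = (112 × 0.05 + 11.2 × 0.20) / 123.2 = 7.84 / 123.2 = 6.4%. The excess falls to 3.6 points.
- u = 10%: 22.4 patients move. Comparator risk = (5.6 + 4.48) / 134.4 = 7.5%. The excess falls to 2.5 points.

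Under these assumptions that contrast understates harm more than the present rule does in any row of the 5% versus 10% example in Step 2.

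**The case against.** Much can be said for the plan as it stands.

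- **Non-exposure is probably small.** Patients have an indication for primary PCI and agree to stenting, the drug is given intravenously, and they stay in hospital while it is given. This stands. It limits non-exposure but does not exclude it, and it makes the lower rows of the range more plausible than the upper ones.
- **Adverse events are recorded with their timing, and causality is judged.** The Adverse events section has the data monitoring committee weigh each event against the time of administration. This helps to separate events before or without dosing, but it does not supply a denominator of treated patients.
- **Low power is not mainly due to this rule.** In the 5% versus 10% example, power is only 32.9% with no dilution at all. This stands.
- **A treated comparison has its own bias.** A patient must survive to the first infusion to enter it, and in an open trial staff may withhold an infusion from a patient who is bleeding. This stands, and it is why the randomized-arm table should be kept.

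A reader might draw three stronger conclusions that the article does not support. One is that the rule always hides harm: Step 3 shows that this holds only if undosed patients have about the control risk. Another is that the 20% in the sample-size paragraph indicates 20% unexposed: that figure is loss to follow-up. The third is that a preoperative-arm patient who reaches PCI before an infusion starts is unexposed: the course runs daily to the seventh day, so a late start is a departure in timing and not an absence of exposure.

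It might also be said that a separate analysis plan can define a safety set. But the article does not leave the matter open. It assigns one population to every safety analysis, so a plan that did otherwise would depart from it.

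**Conclusion.** The point holds in a limited form. The stated rule keeps never-infused Danhong-assigned patients in the Danhong safety denominators, and the design makes such patients possible, especially in the postoperative arm.

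The size cannot be derived from the article. It is nil if every assigned patient receives at least one infusion and small if only a few per cent do not. It becomes material only at 10–20%, a level for which the article gives no evidence. The direction is also open: towards no difference if undosed patients resemble controls, towards apparent harm from Danhong if they are sicker. In either case the table does not describe risk in patients who received the drug.

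This justifies an additional safety analysis. It does not justify replacing the randomized comparison, and it does not touch efficacy.

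**What to change.** Keep intention-to-treat for efficacy, and keep the safety table by randomized arm. Amend the population sentence to add a pre-specified safety set, reported beside that table for bleeding, adverse events and blood tests:

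- **Danhong group:** patients with at least one Danhong infusion, grouped by treatment received, with the timing of the first infusion shown.
- **Comparator:** control-arm patients who received conventional treatment without Danhong.
- **Listed separately:** Danhong-assigned patients who were never infused, with their events. They are not pooled with control.

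The cost is one sentence and one extra set of tables. Sample size and treatment are unchanged. The drawback is that the treated comparison is not fully protected by randomization, since patients must survive to the first dose, so the text should say that the two tables are to be read together. If everyone is treated as assigned, they will agree.

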### Quality management

Study physicians and evaluators will be trained in SOPs in advance. The ECG and angiographic images from a subcenter should be sent to the data center for unified blinding evaluation to obtain high-quality research data. The accuracy, reliability, and abnormal judgment criteria of laboratory tests should be unified in each research center.

